### Sample size

The study will aim to recruit 150 children from 10 schools (15 children at each school site), thus, five schools with a total of 75 children in the PiP intervention arm and five schools with a total of 75 children in the control arm. At least four clusters per arm are recommended for a cluster RCT [50] and this sample size exceeds recommendations for pilot trials [51]. Therefore the sample will be sufficiently large to provide clear estimates of recruitment and follow up.

### Trial arms

#### Usual practice arm (control)

Families allocated to the usual practice arm will not have access to a playground intervention and will continue with their daily routines as usual.

### PiP intervention arm

#### Development of the intervention

The UK CMO's guidance for physical activity in the under 5-year-olds [28] and existing literature was reviewed [32,41-43]. The predominant behavioural change theory used in successful childhood obesity prevention interventions [24] was Bandura’s SCT [33,34], therefore, the SCT was used to direct the intervention development. Additionally, six focus groups with a total of 17 White and Pakistani mothers and caregivers (English and Urdu speaking) explored typical physical activity in toddlers and the barriers to and facilitators for physical activity [52]. Mothers reported that their children were innately active and enjoyed playing outside. Lack of time was a major barrier to physical activity. Mothers minimised the number of journeys they took and were put off organised activity sessions, finding it inconvenient to leave the house with young children. Other barriers to outdoor physical activity included feeling that their neighbourhood was an unsafe place to play outdoors and needing help from another adult to take the children to the park. Additionally the season, weather, and having to take public transport to parks were also identified as barriers. Some key facilitators for physical activity were having someone to help during activities and having activities available locally. There was little variation in the reported barriers and facilitators between ethnicities. Using these sources of information, a manual and materials to deliver PiP sessions were developed. These were reviewed by five early-years workers and minor revisions were made.

### Delivery of the intervention

Primary school/Children's Centre playgrounds will be made available to parents and pre-school children at times when parents are likely to be attending school (for example, dropping off or picking up older children from school, or young children from nursery). These times have been chosen in order to capitalise on times of the day that parents are already out of the house and will minimise the number of journeys to activities that parents have to make (identified as a barrier in focus groups). Six PiP sessions per week for 30 weeks (three school terms) will be available to families. This number of sessions was chosen to meet the need for flexibility, which was highlighted at the focus groups. Families will be encouraged to attend at least three of these sessions each week. Each PiP session will last for 30 minutes and include play activities likely to be of light activity and MVPA. There is some evidence to suggest that as little as an extra ten minutes per day of MVPA significantly reduces fat mass [2]. Furthermore, 56 minutes of MVPA per day in boys and 42 minutes in girls aged 5 to 8 years has been reported to improve metabolic status assessed from a composite score of various cardiovascular disease risk factors [53]. Given the sporadic nature of physical activity in these very young children, and given that between 25 and 70% of total physical activity in pre-schoolers has been classified as MVPA [22,54,55], it is likely that during a 30-minute session, the children will spend at least 10 minutes in MVPA. This will contribute towards the amount of MVPA required for health benefits.

There will be two phases to the intervention. The initiation phase (10 weeks) will be facilitated by parent involvement and/or early-years workers employed by schools/Children’s Centres. These facilitators will undertake a 2-hour training session using the PiP manual and will be accompanied during the first session by the researcher (SB) who developed the PiP intervention. Subsequent telephone support from the researcher will be offered to facilitators during the intervention period. The PiP session in the initiation phase consists of two, 5- minute structured parent-and-child play sessions and 20 minutes of free play. Further details of the intervention are given in Table 1. During the maintenance phase (20 weeks) playgrounds will remain available six times a week (three mornings and three afternoons) to parents and their pre-school children for 30 minutes at specific times coinciding with the so-called school run, allocated by the school/Children's Centre. For the purposes of the pilot trial, the facilitator (parent involvement and/or early-years worker) from the initiation phase will take a register of attendees at the beginning of the sessions but will not give formal supervision during the session. Table 1 illustrates the content, evidence for the content and associated behavioural change techniques for both the initiation and maintenance phase of the intervention.

**Table 1 T1:** Content of the initiation and maintenance phases of the PiP intervention, the evidence to support the content and the behavioural change techniques used

**Content**	**Initiation (I) maintenance (M) phase**	**Evidence to support content**	**Behavioural change technique**
Provision of playground area at a time which coincides with families' daily routines (dropping off/picking up at school/nursery)	I, M	SCT (environmental factor) ^24, 25^	Environmental changes
		Focus group reports: activity sessions need to fit into other daily routines ^*47*^	
Provision of outdoor play equipment during sessions	I, M	SCT (environmental factor) ^24, 25^	Environmental changes
Facilitator to give telephone support and encourage families to attend the sessions	I, M	SCT (behavioural factor) ^24, 25^	Social processes of support/encouragement
Group sessions	I, M	Recommendation for pre-school obesity interventions ^23^	Social processes of support/encouragement
Supervision at the session from the facilitator	I	Focus group reports: parents need extra support to feel confident and safe playing with their children outside ^47^	Social processes of support/encouragement
Facilitator to encourage children to be physically active and give rewards (praise and “well done” stickers)	I	SCT (behavioural factors) ^24, 25,^ Recommendation for pre-school obesity interventions ^35^	Social processes of support/encouragement
Facilitators support parents to give positive reinforcement to their children’s physical activity	I	SCT (behavioural factors) ^24, 25^ Parent involvement is important for children’s behavioural change ^33, 34, 35^	Modelling Social processes of support/encouragement Increasing skills Rehearsal of skills
Facilitator to encourage outdoor play between parent and child outside of the intervention	I	CMO report ^13, 35^	Social processes of support/encouragement
Facilitator to provide information (verbally), give leaflets and facilitate parent discussions on the link between physical activity and health, guidelines for physical activity and sedentary behaviour in under 5-year-olds	I	SCT (personal factors) ^24, 25^	Provide information regarding behaviour
		Recommendation for pre-school obesity interventions ^23^	
			Information on consequences
			Social processes of support/encouragement
Ideas for active play provided and activity is playful	I (facilitator) M (instruction cards)	SCT (personal factors) ^24, 25^	Increasing skill
		CMO report ^13,^ Recommendation for pre-school obesity interventions ^35^	Skill rehearsal
			Modelling
			Graded tasks
Facilitator teaches two 5-minute structured parent and child games to develop child’s observational learning, locomotor, stability and object control skill	I	SCT (personal factors) ^24, 25^	Increasing skill
		CMO report ^13^	Skill rehearsal
			Modelling
			Graded tasks
Facilitator modifies play activities to suit the different needs of children in the group	I	CMO report ^13^ Recommendation for pre-school obesity interventions ^35^	Graded tasks
Children have 20 minutes free play	I	CMO report ^13^	Environmental changes
Facilitators to ensure regular infusions of different play equipment during free play	I	Recommendation for pre-school playground interventions ^33^	Environmental changes
Play equipment given out once a week to support families to play at home	I (3 schools only)	SCT (environmental factors and behavioural factors) ^24, 25^	Rewards/incentives
			Skill rehearsal
		CMO report ^13^	

PiP, pre-schoolers in the playground; SCT, social cognitive theory; CMO, Chief Medical Officer, superscript numbers denote the supporting reference.

### Outcome measures

In order to assess the feasibility of a full-scale cluster RCT of the PiP intervention, this pilot trial will examine recruitment rates, attendance and attrition, acceptability of the trial procedures and of the PiP intervention to parents, fidelity of intervention implementation; and capability and capacity for schools to deliver the intervention. Health outcomes and the feasibility of the tools used to measure these outcomes will also be assessed.

### Recruitment

The following will be recorded:

● Number of eligible children screened and agreed or declined further contact about the study

● Number of exclusions

● Number of parents of children who agreed to further contact about the study and are contacted or unable to be contacted

● From those parents who are contacted, the number who declined, missed the recruitment window (that is, the intervention/control period had already begun before they arranged an appointment for baseline measures) or were given an appointment for baseline measures

● Number that fail to attend the appointment for baseline measures, attend the appointment and do not consent, or attend and give consent

### Attendance and attrition

The following will be collected:

● Attendance rates at PiP sessions

● Who attends the PiP session with the child

● Attendance to measurement sessions (at baseline, 10, 30 and 52 weeks)

● Attrition (to both PiP and measurement sessions)

### Acceptability of the trial and the PiP intervention to parents

A purposive sample of 20 parents will be recruited to the qualitative component of the study. Selection will be on the basis of role (for example, mother, father, grandparent, or carer), ethnicity and whether an attender or drop-out. We will select 15 parents/carers from the intervention arm and five from the control arm. This maximum variation sampling approach [56] will ensure a wide range of views are collected. Parents will be interviewed after completing their 10 week data collection. Semi-structured interviews will explore the acceptability of PiP (intervention only) and their experience of taking part in the trial e.g. randomisation, measurement tools, and incentives (intervention and control). All interviews will be conducted using a topic guide to ensure consistency, although the format will be flexible in order to allow participants to generate naturalistic data on what they see as important. They will be audio-recorded digitally and transcribed verbatim.

### Fidelity of intervention implementation

Fidelity will be assessed in line with guidance from the NIH Behavior change Consortium [57]. To assess the fidelity of training for PiP facilitators, the trainer will be asked to reflect after sessions and complete a short form detailing the percentage of training delivered exactly as intended, and record any adaptations made to training. PiP facilitators will also complete a short evaluation form at the end of the training session to ensure provider skill acquisition.

To monitor the delivery of the intervention three sessions at each intervention school (two in the initiation and one in the maintenance phase) will be observed. A standardised form will be used for each observation where the observer will score PiP facilitators on a scale of 1 to 4 (1 being poor adherence to the intervention protocol and 4 being complete adherence to intervention protocol) for five key intervention factors (delivery of PiP as per the manual, supervision, support given to parents, encouragement of children, and infusion of play equipment). To monitor the number of sessions provided each week during the initiation phase of the intervention, PiP facilitators will be asked to complete a short form at the end of each session detailing whether the session was provided, the number of attendees to the session and the structured play activities provided at the session.

### Capability and capacity for delivery

At 10 weeks, the parent involvement/early-years workers who have delivered the intervention will be interviewed to explore the feasibility of the delivery and help refine the nature and content of intervention. At 30 weeks (after the maintenance phase) we will conduct telephone interviews with head teachers at schools in the intervention arm to explore their views on the acceptability of the intervention within the school setting, in particular the impact of PiP upon the school day. Both sets of interviews will be audio-recorded digitally and transcribed verbatim. A description of each school’s playground environment including size, availability of equipment/facilities/markings will be recorded along with the schools local environment (for example, proximity to other outdoor play space).

### Health outcomes

The following outcomes will be assessed at baseline, 10 weeks, 30 weeks and 52 weeks: for the child, daily time spent in physical activity, body mass index (BMI), waist and upper-arm circumferences and health-related quality of life; for the parent, health-related quality of life, self-efficacy and wellbeing.

#### Physical activity

Children will wear a triaxial, Actigraph GT3X+ accelerometer, (15 second epochs; Actigraph Pensacola, FL, USA) on a belt around their waist (anterior to the iliac crest) during waking hours for six days, including at least one weekend day [58]. Parents will be provided with a diary to record the times that the accelerometer is put on and taken off their child. Data will be downloaded and reduced using Actilife software version 5 (Actigraph). Non-wear time will be defined as consecutive zero counts of ≥ 10 minutes [59]. Parent-completed wear-time logs will be checked for periods when the monitor was not worn, and will be matched against Actigraph data. To determine the minimum wear time (that is, daily-wear hours and number of wear days) required to achieve a reliable estimate of habitual physical activity, that is, intraclass correlation coefficient (ICC) value ≥ 0.8 [60], the Spearman-Brown prophecy formula will be applied to participants' baseline accelerometer data.

Vertical axis activity counts will be converted to time spent sedentary (≤ 37 counts per 15-second epoch [61]) in light physical activity, (38 to 419 counts per 15-second epoch in MVPA (≥ 420 counts per 15-second epoch and in total physical activity (light to vigorous; ≥ 38 counts per 15-second epoch). The cutpoints derived by Pate et al. [61] for children aged 3 to 5 years old were selected as they have been cross-validated under free-living conditions and have been found to have better agreement with directly observed physical activity than other published Actigraph intensity cutpoints in children aged 16 to 35 months [62]. Daily physical activity energy expenditure will be calculated using the Actilife software (Version 6). Additionally, the percentage of children meeting physical activity guidelines of 180 minutes per day [28] (including light, moderate and vigorous physical activity) will be calculated.

### Anthropometry

Body mass will be measured in standard clothing conditions (lightweight clothing), using regularly calibrated Seca electronic scales (Medical Scales and Measuring Systems, Birmingham UK). Height will be measured using a Leicester Height Measure (Harlow Healthcare Limited,HarlowUK). Waist circumference will be measured at the midpoint between the lowest rib and the iliac crest. Upper arm circumference will be measured at the midpoint between the acromion process of the scapula and the olecranon process. Body mass and height will be used to calculate BMI, these will be converted to age- and sex-adjusted *z*-scores relative to the World Health Organization (WHO) 2006 growth standard using the least mean squares (LMS) method. Percentage of overweight children in each arm (intervention or control) will also be recorded and defined as having a BMI z-score greater than +1.04 (= 85th centile).

### Health related quality of life and well-being

The child’s health-related quality of life will be assessed using the Paediatric Quality of Life questionnaire (PedsQL; infant or 2- to 4-year-old version). The PedsQL infant and toddler scales are reliable, valid and have good internal consistency (≥ 0.7) [63]. Parental health-related quality of life will be assessed using the EQ5D, this self-complete standardised instrument is validated for use and is reliable for adult populations (convergent validity: Spearman rank order coefficients with WHO-5 sum-scores = 0.49; [64]). Parental wellbeing will be assessed using the Comprehensive Quality of Life Scale-Adult (ComQol-A5) [65]; it is a valid and reliable scale (Cronbach’s Alpha = 0.39 for all seven domains [66]) that is designed to be used with any section of the adult population. Parental self-efficacy will be assessed using the General Self Efficacy Scale; the scale is valid for use in a general adult population and has excellent reliability (Cronbach’s Alpha > 0.80) [67].

### Injuries and health service use

Number and type of injuries sustained during the intervention/usual care period and the consequence of the injury (that is, medical attention from General Practitioner, or hospital visit) and service use (health and social care) will be reported by parents and recorded at each assessment point using previously developed questionnaires.

### Feasibility of the measurement tools

The feasibility of using all of the measurement tools in a full trial will be assessed; this is important to predict the success of a full-scale trial and to ensure that the trial is not too burdensome for participants. Using accelerometry to measure physical activity will be assessed by examining the number of participants who meet the criteria for inclusion in data analysis. The feasibility of measuring BMI, and waist and upper arm circumference will be assessed by the percentage of data collected. The feasibility of using the following questionnaires will be assessed by examining completion rates: for children, infants (13 months to 2 years old) and toddlers (2 to 4 years old), the PedsQL; for parents, the EQ5D, ComQol-A5 [67] and General Self Efficacy Scale [67].

### Data to inform sample size calculation

An important aspect of the pilot study is to collect data to estimate the sample size required for a full RCT. The pilot RCT will provide data on the variability of outcome measures; estimates of effect sizes between control and intervention, and estimates of ICCs which are currently unavailable from other studies. It will also provide a more accurate estimate of the follow-up rate.

### Data analysis

#### Statistical analysis

For both arms the numbers of schools and children screened, randomly assigned, receiving PiP or usual care, completing the study protocol, and providing outcome data will be summarised. The number of children withdrawing from the intervention and/or the trial, and where available the reasons for withdrawal, will be summarised by arm. For each data collection point the number of non-attenders will be calculated for each arm and attendance rates compared.

Whilst the main aim of this study is to establish practicality, feasibility, recruitment rates and samples size in order to inform a full-scale trial, and although it is unlikely that the small sample size will result in effectiveness being established, the primary outcome for a full trial, daily MVPA, will be analysed to mimic practice in a full-scale trial. Results from this analysis will be treated as preliminary and interpreted with caution [68,69]. As the number of clusters is low, cluster summary statistics will be utilised rather than multi-level modelling [70,71]. The analysis will be carried out using the school as the unit of analysis and the mean MVPA per day for the individuals in the school as the outcome variable. A weighted linear regression model will be used to compare the intervention and usual-care arms weighted by the number of participants followed up in each cluster and adjusted for the baseline average MVPA per day for each cluster. We acknowledge that participation in a physical activity trial may in effect be an intervention in itself for the control group. Therefore the difference in health outcomes (physical activity and anthropometry) between the intervention and control arms will provide meaningful data on the potential effectiveness of the intervention. We will assess whether playground environment and local environment have a significant impact upon intervention uptake, attendance and changes in levels of physical activity. If they are found to be significant we will consider stratifying schools according to their environment in the full trial.

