### UK physical activity policy for pre-school children

The importance of engaging pre-school children in daily physical activity was brought to the forefront in July 2011 with the publication of the UK’s first physical activity guidelines for children under 5-years-old in the Chief Medical Officer’s (CMO) report *start active, stay active*[28]. The report recommends 180 minutes of physical activity (light, moderate and vigorous intensity) each day, and states that the volume of physical activity is more important than the intensity. Physical activity should be spread throughout the day and include active play (activities that involve movements of all the major muscle groups), and the development of locomotor, stability and object-control skills.

These guidelines are a significant step in recognising the importance of physical activity promotion for pre-school children; however, guidelines themselves do not change behaviour. The determinants of physical activity in young children are unclear; one systematic review that studied correlates of pre-schoolers’ physical activity found that boys were more active than girls and that parents’ levels of physical activity and a child’s time spent outdoors had a positive association with physical activity [29]. Additionally, preliminary findings from an ongoing systematic review suggest that providing easy-access environments that facilitate physical activity are important [30]. The CMO report states that a ‘concerted and committed action to create environments and conditions that make it easier for people to be more active is needed [28, page 8]. The guidelines highlight the need for activities to promote movement in the early years and recognise that local communities can have a strong influence on behaviour. The report suggests investment in community level programmes in settings such as school playgrounds. We therefore aim to develop and evaluate such an intervention in an area of ethnic diversity and social deprivation in West Yorkshire, UK.

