### Randomisation and blinding

Randomisation will be carried out by York Trials Unit Randomisation Service using a secure computer system. Once baseline data have been collected, participating schools will be randomly allocated to one of the two arms, PiP intervention or usual care (control), on an equal basis (that is, five schools in each arm). Since ethnicity may be an important predictor of physical activity [11] and thus, to avoid chance imbalance in ethnicity, schools will be stratified and blocked by ethnicity (> 50% South Asian pupils or > 50% White pupils).

Blinding of the trial coordinator, schools, participants, and parent-involvement workers/early-years staff will not be possible. The community research assistants who will be assessing outcome measures will be blinded to each school’s allocation as will the statistician and health economists performing the data analyses.

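### With ten schools, the stated MVPA model omits the randomisation stratum and each child's own baseline, so its interval is usually wider than the collected data allow

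*Protocol article*

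**What the plan says.** Under Randomisation and blinding, the protocol says that "schools will be stratified and blocked by ethnicity (> 50% South Asian pupils or > 50% White pupils"). The reason it gives is this: "Since ethnicity may be an important predictor of physical activity". Baseline data are collected before schools are allocated, five to each arm.

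Under Statistical analysis, daily MVPA is analysed "using the school as the unit of analysis and the mean MVPA per day for the individuals in the school as the outcome variable". The regression is "weighted by the number of participants followed up in each cluster and adjusted for the baseline average MVPA per day for each cluster". Arm and the school's baseline average are the only terms named.

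The same section chooses cluster summaries over multilevel modelling because there are few clusters. It says that the analysis is meant to mirror what a full trial would do and that the results are preliminary.

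**The concern.** Two features of the design and data go unused.

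- **The stratum.** Blocking on ethnicity removes most of the ethnicity difference from the arm contrast. If the stratum is then left out of the model, any ethnicity effect that the baseline mean does not explain stays in the residual. The standard error then overstates the uncertainty.
- **The child's own baseline.** The slope on baseline is estimated from ten school means, although every child is due to have a baseline accelerometer measurement. Age (an eligibility criterion, 18 months to 4 years) and sex (needed for the BMI z-scores) are also available. The Background cites a review in which "boys were more active than girls".

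What is at stake is precision in a ten-unit analysis, and the quality of the template that it passes on to the full trial.

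**Working it through.** **Inputs from the protocol.** There are 10 schools with 15 children each: 10 x 15 = 150, and 5 x 15 = 75 per arm, which reproduces the stated sample size. The protocol gives no alpha, SD, ICC, correlation or effect size, and says that ICCs are not available from other studies. It therefore contains no interval width to reproduce, and the comparison has to rest on assumptions.

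**Degrees of freedom.**
- Stated model (intercept, arm, school baseline mean): 10 - 3 = 7, t = 2.365.
- Stated model plus stratum: 10 - 4 = 6, t = 2.447. The multiplier alone grows by 2.447/2.365 = 1.035, or 3.5%.
- Two-stage with stratum (intercept, arm, stratum at the second stage): 10 - 3 = 7, the same as the plan.

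**Main simulation.** True effect 0; 5 v 5 schools blocked within stratum (splits 4/6, 5/5, 6/4); 15 children per school; 80% followed up; ICC 0.02 to 0.10; child-level baseline/follow-up correlation 0.2 to 0.8; school-level correlation 0.2 to 0.9; 2,000 to 2,500 runs per setting. The ethnicity effect is the effect on follow-up beyond baseline, in child-level SDs. Entries in the two middle columns are the mean 95% half-width divided by that of the stated model.

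| Ethnicity effect | Stated model + stratum | Two-stage + stratum | Coverage of stated model |
|---|---|---|---|
| 0 | 1.04-1.07 | 0.92-0.99 | about 0.95 |
| 0.3 SD | 0.76-0.97 | 0.68-0.90 | 0.95-0.98 |
| 0.5 SD | 0.57-0.87 | 0.51-0.78 | 0.97-0.996 |

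The two-stage analysis with stratum covered 0.93 to 0.96. It was narrower in every setting: by 1-8% with no ethnicity effect and by 10-32% at 0.3 SD. The smallest gain (ratio 0.992) came with child-level correlation 0.2, school-level correlation 0.9 and ICC 0.10. Using the child's own baseline without the stratum gave ratios of 0.89 to 0.98, so this part of the gain does not depend on ethnicity.

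**Unequal schools.** 9-21 children per school, 25% attrition, ICC 0.05, child-level correlation 0.5, modest age and sex effects, 4,000 runs. Half-widths in SD units:
- No ethnicity effect: 0.510 v 0.460; 0.460/0.510 = 0.90. Type I error of the stated model 5.1%.
- Equal gap at both times: 0.515 v 0.460; ratio 0.89. Type I error 4.8%.
- Widening gap: 0.566 v 0.460; ratio 0.81. Type I error 3.6%.
- Gap at follow-up only: 0.612 v 0.461; ratio 0.75. Type I error 3.1%.

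If the school baseline average is taken over followed-up children only, the stated model's half-width with no ethnicity effect is 0.489, and the ratio becomes 0.460/0.489 = 0.94.

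**Missing baselines.** 78% follow-up, ICC 0.02-0.10, child-level correlation 0.5, school-level correlation 0.7. With complete baselines the two-stage interval is 9-12% narrower when there is no gap or an equal gap. With a widening gap it is 21-27% narrower, and the stated model's type I error is 2-3%. If 20-30% of baselines are missing and those children are dropped, the no-gap or equal-gap gain falls to about 1-7%. Filling the missing baseline with the school mean plus an indicator keeps it near 10-13%.

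**The case against.** The strongest reply is that the stated analysis is a recognised and valid choice for few clusters, that its results are declared preliminary, and that no stated progression decision uses this interval. All of that stands, and it limits the weight of the point.

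Several stronger readings are tempting, but the protocol does not support them.

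- **That the interval is necessarily miscalibrated because ethnicity predicts activity.** The Background reports lower activity levels among South Asian school-age children. That is a difference in level, not in change. A gap that is equal at baseline and follow-up is largely absorbed by the school baseline mean (type I error 4.8%, half-width 0.515 against 0.510).
- **That the trial risks bias or false positives.** The error, where it occurs, is conservative.
- **That the stratum should simply be added to the stated model.** This costs one of seven degrees of freedom and widens the interval by up to about 7% if ethnicity adds nothing beyond baseline. It begins to help only at roughly 0.2 SD. Leaving it out of a one-stage, ten-point regression is defensible.
- **That the baseline and follow-up means describe different children.** The protocol does not say which children enter the baseline average, so this cannot be asserted.

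A fair practical objection is that a child-level baseline may be missing. The protocol treats the number of children with analysable accelerometry as an open feasibility question. Dropping those children would remove much of the gain, so the fix has to deal with it.

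**Conclusion.** The point holds as one of efficiency, with conditional and conservative miscalibration. The stated model omits the factor used to randomise and reduces child-level baselines to ten means, so its interval is usually wider than the same data allow.

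The gain from a two-stage analysis with stratum is about 1-12% in half-width if ethnicity does not predict change beyond baseline. It is about 10-30% if ethnicity does so at around 0.3 SD or through a widening gap, and more for larger effects. In those moderate cases the stated test's type I error is roughly 2-4%.

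These figures assume ICC 0.02-0.10, child-level correlation about 0.5 (0.2 to 0.8 in the widest grid) and about 20-25% attrition. None of these is given in the protocol. The omission itself needs no assumption; it can be read directly from the two sections. Practical weight is moderate: the analysis is preliminary, but it is offered as a model for the full trial.

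**What to change.** Keep the cluster-summary approach and restate it in two stages.

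1. Regress each followed-up child's daily MVPA on own baseline MVPA, age and sex, ignoring arm. Where the baseline is missing, insert the school's baseline mean and add a missing-baseline indicator, so that no followed-up child is dropped. Baseline is measured before schools are allocated, so whether it is missing cannot be a result of the allocation.
2. Compare school-mean residuals between arms by linear regression, weighted by the number followed up, with the ethnicity stratum as a term and 7 degrees of freedom.

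Do not adjust for follow-up wear time by default, since it is measured after randomisation. Do not settle for adding the stratum to the one-stage model.

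The cost is a revised sentence or two and slightly more analysis code. No new data are needed and no degrees of freedom are lost relative to the plan. The trade-off is greater reliance on a usable child-level baseline.
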